#### Qualitative data

To further understanding of the patterns of primary and secondary outcome data, participants (if feasible) and their caregivers will be asked to participate in a 45 minute in-depth interview as part of the 1 year post-transfer data collection period. In addition to exploring changes in health and social services, guided, semi-structured questions regarding the transition experience (e.g., experience with continuity of care, preparation for transfer, health, social participation, and their recommendations) will be posed. Such an approach will help foster flexibility and is particularly well suited to exploring the transition process. Although this is a semi-structured format, participants will be encouraged to talk freely about their experiences.

### Data collection

#### Study timeline

The inclusion of three different disability groups raises the possibility of differences arising as a function of disability-related influences rather than the transition intervention. To offset this possibility, baseline measures will be sampled twice to document existing differences within the three prospective participant groups and reduce individual variability, resulting in three different data collection periods for ABI and CP groups (Table 
2). The first baseline will occur at 17 years of age and correspond to the completion of year 1 of LIFEspan. The second will occur at 18 years of age, just prior to discharge, corresponding to the end of year 2 of LIFEspan. Follow-up measurement of outcomes of interest will occur at 19 years of age and correspond to 1 year post-transfer. Additionally, participants will be contacted bi-annually to complete specific survey materials (i.e., community involvement and allied health care surveys) to ensure a short window of recollection. SB group data will also be collected at these age markers, though this group will not have had exposure to LIFEspan. For retrospective participants, once consent is received, the ABI/CP participants will be ‘followed’ for a three-year period preceding introduction of the LIFEspan model. This window will match the age-related collection periods outlined for the prospective participants (i.e., first and second baseline, and post-transfer).

**Table 2 T2:** Timeline of the Study

**Protocol Events**	**Timeframe**		
	**Year 1**	**Year 2**	**Year 3**
	**Baseline 1**	**Baseline 2**	**Outcomes**
	**Age: 16-17**	**Age: 17-18**	**Age: 18-19**
	**1 Year Pre-Transition**	**Transition Year**	**1 Year Post-Transition**
***Recruitment and Consent***	☑		
***Demographic Questionnaire Form***	☑		
***MOHLTC Billing Summaries***	☑	☑	☑
▪ Medical Specialists			
▪ Family Doctor			
▪ Emergency Services & Hospitalizations			
***Chart Audit***	☑	☑	☑
▪ LIFEspan Service Delivery Description			
▪ Demographics, Functional Level, & Diagnoses			
▪ Medical Specialists			
▪ Hospital Allied Care			
***“Allied Care” and “Community Involvement” Forms***	☑	☑	☑
▪ Community Allied Care	+ 6-months follow-up	+ 6-months follow-up	+ 6-months follow-up
▪ Vocation, Recreation, Social Activities, & Sports			
***Self-Reported Secondary Measures***	☑	☑	☑
▪ Transition Readiness			
▪ Health Status & Well-Being			
▪ Participation			
***Youth and Parent Interviews***			☑
▪ Transition Preparation & Experience			

#### Quantitative data

LIFE-H, HUI3, AQoL, and Arc assessment tools have been designed for use with individuals with disabilities; and thus, have low reading levels and do not include abstract questions that might be challenging to adolescents
[19]. PIH and Self-Efficacy questionnaires are being trialed for the first time with the populations of participants enrolled in the study. Clinicians working with these participant groups have reviewed the tools for potential issues in comprehension. In addition, it will be emphasized to the participants that unlike school tests, the questions on these surveys have no right or wrong answers. Considerations of special accommodations, such as the provision of additional time, convenient locations, and functional and/or communicative assistance, will also be made, in accordance with recommendations in the literature
[58]. Despite the potential for bias, completion by proxy respondents (e.g., parents, caregivers) will be sought where participants are unable to complete the measures by means of self-report. In these circumstances, parents’ views may be equally valuable as they will continue to play a significant and active role in managing the young person’s health care transition.

The amount of time required for the data collection process is expected to range from 1 to 4 hours, depending on the participants’ needs and accommodations required for completing the assessments based on their level of functioning. Secondary mail-outs and follow-up phone calls are expected to be required in most cases. In the event of missing information or uncompleted questionnaires, follow-up phone calls will be made. As personal claims histories will be generated by the MOHLTC in hard-copy format, study personnel will code and manually enter this information along with all data collected during the annual and bi-annual participant sessions. Each participant will be assigned a unique identifier to anonymize their data and facilitate linkage of the multiple data sources within a master spreadsheet. Since all data will be manually entered, we will ensure the accuracy of data by entering numerical data from all questionnaires twice, and establishing a 90% inter-rater reliability on 20% of chart audit entries and MOHLTC data that require coding.

#### Qualitative data

During the semi-structured interviews, participants will be provided with a hand-held stop-and-go sign they can use when they feel comfortable going ahead with the next question or stopping when they do not wish to answer a question. The use of such images may help minimize the adult-child (or experimenter/participant) power differential and ensure that participants feel comfortable and in control at all stages of the interview. The interviews will be digitally recorded to permit verbatim transcription. For the first 4 to 6 interviews, research team members skilled in qualitative interview techniques will review the transcripts and modify the interview guide as required. This process will highlight questions that require repeated clarification or rewording; identify new questions that may need to be posed; and allow a refinement of the script that is in keeping with a more natural conversation. We will verbally inform these first few participants that we are piloting the interview to ensure that ‘we are asking the right questions in the right way’. They will also be informed that we may follow-up and ask if they would be willing to respond to a few additional questions if significant changes to the script are made. This would be done by phone; if participants verbally consent, their answers will be recorded and included with their original interview transcript.

### Power calculation

Based on Young et al.’s study
[13], we expect that 25% of young adults transferring from pediatric to adult services will meet our continuity of care definition (i.e., at least one visit to a primary care provider during the first year post-transition). It is hypothesized that the LIFEspan model will increase continuity of care to 75% in the intervention group (i.e., a three-fold increase). A sample size of 88 youth for the prospective comparison (70 Intervention and 75% continuity of care versus 18 Comparison and 25% continuity of care) will provide 90% power to detect this difference at an alpha level of 0.05. A similar retrospective group will also be required. Given the large sample size, the comparison between the prospective and retrospective group of participants with ABI and CP will also have very high power to detect this clinically important difference.

### Data analyses

#### Quantitative analyses

The audit information collected about each visit will be entered into a statistical software package (SAS®) and will include categorical data (yes/no), frequency counts, and calculated percentages. SAS® software will be used to conduct a descriptive analysis and generate graphical representations, measures of central tendency, and calculations of confidence intervals. This analysis will compare actual practice with practices proposed in the LIFEspan model. A similar analysis will be conducted comparing practices in the LIFEspan model to the standard of care model. For the subset of variables that are subject to participant variability, further analyses using polytomous logistic regression will compare service provided by degree of disability and diagnosis to identify factors associated with greater or lesser than expected use of services predicted by LIFEspan. Because of the large number of comparisons this entails, the analysis will be limited to univariate models and will be exploratory in nature. Rather than reporting p-values as being greater or lesser than .05 or .01, we will report the exact p-values.

Using SAS® software, multiple regression (health, well-being, social participation, and transition readiness scales), logistic regression (continuity of care and community involvement) and Poisson regression (health care utilization) analyses will be conducted to determine if there are differences between the intervention and comparison groups after controlling for disability, severity, basic demographics (e.g., SES, gender), and baseline data on both the outcome of interest and other baseline measures, taking into account within subject correlations. Planned contrasts will be used to compare outcomes for the intervention group with the prospective SB group as well as comparing outcomes for the intervention group with the retrospective ABI/CP group. A within intervention comparison between LIFEspan ABI and LIFEspan CP will also be conducted.

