The intervention group will consist of 30 youth with ABI and 50 youth with CP enrolled in LIFEspan. The two comparison groups will consist of youth not enrolled in this service model: 21 youth with SB (prospective cohort) and 15 young adults with ABI and 20 with CP (retrospective cohort). Data from each participant group will be collected from a matched window of time, corresponding to the participants’ 16^th^ to 19^th^ birthday. All parents of participants from the prospective groups will be eligible to participate as secondary participants in a qualitative component of the outcome evaluation. Recruitment for this component will be built into recruitment of the primary study participants.

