[48] and a survey on community involvement, developed for the study, will be used to assess social participation. However, currently there are no measures available regarding youths’ transition readiness; that is, their capacity to navigate the adult system as a function of transition preparation. Thus, to provide an approximation of this capacity, Arc’s Measure of Self-Determination (capacity to determine their own fate)
[46], Self-Efficacy for Managing Chronic Disease (capability to perform in a goal-directed manner)
[53], and Partners in Health (PIH) self-management questionnaire (the ability to participate in the management of one’s health condition)
[45] will be used. All standardized measures selected for the study have good psychometric properties
[45,46,51-57].

Finally, a chart audit tool will be used to abstract information from medical records and to comprise a master record for all visits made during the identified timeframe for each clinical group. The audit tool will include basic demographic data such as date of birth, gender, disability diagnosis, severity, and level of functioning (e.g., Gross-Motor Function Classification System). Cognitive level and educational status, communicative ability, ambulation status, and living arrangements will also be noted if information had been documented in the chart. An additional demographic questionnaire will also be completed by the participants and capture similar information. With respect to service delivery, data including visit dates, discussion of key domains, health care professionals seen and referrals made, discharge summary, date of discharge/transfer, name of primary care provider, and name of follow-up provider will be collected. This information will provide a comprehensive description of the transition services received by the participants as part of the process evaluation, and will serve to explain the trends that emerge in the outcome evaluation.

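### In the exploratory service-provision analysis, restricting to univariate models saves no tests for the two named factors and may leave diagnosis and severity entangled

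*Protocol article*

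**What the plan says.** The point concerns the first paragraph of Quantitative analyses (under Data analyses) in the protocol article, which covers the audit data of the process evaluation. After a descriptive comparison of actual with intended practice, it adds a modelling step: "For the subset of variables that are subject to participant variability", it plans that "further analyses using polytomous logistic regression will compare service provided by degree of disability and diagnosis". The purpose is "to identify factors associated with greater or lesser than expected use of services predicted by LIFEspan". The restriction follows at once: "Because of the large number of comparisons this entails, the analysis will be limited to univariate models and will be exploratory in nature". On reporting, it says that "we will report the exact p-values" instead of classing results as above or below .05 or .01.

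Three other places bear on this:

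- Participants: "The intervention group will consist of 30 youth with ABI and 50 youth with CP enrolled in LIFEspan".
- Measures, Quantitative data: the chart audit tool abstracts diagnosis, severity and level of functioning.
- The second paragraph of Quantitative analyses: the outcome models, including the Poisson model for health care utilization, control for disability and severity together.

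**The concern.** The number of comparisons is given as the reason for using univariate models. With only two factors named, fitting them one at a time produces as many factor tests as fitting them together, so the reason does not support that part of the choice.

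The restriction may also work against the purpose. If each model holds one predictor, and severity is distributed differently in ABI and CP, the diagnosis result absorbs part of any severity effect and the severity result absorbs part of any diagnosis effect. The article says that audit information will help to explain trends in the outcome evaluation. A reader could then take a severity pattern in service provision for a diagnosis pattern, or the reverse, when interpreting how LIFEspan was delivered. The stake is the interpretation of a side analysis, not a primary or secondary conclusion.

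**Working it through.** The article gives no figure for this analysis, so there is none to reproduce.

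**1. Number of tests.** Inputs: two named factors (article); K service variables (not stated, assumed 5 to 40).

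- One-factor models: 2 models × K variables = 2K factor tests.
- One joint main-effects model per variable: 2 factor tests × K = 2K.

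Treating tests as independent at 0.05, the chance of at least one false positive is 1 − 0.95^(2K), the same under both approaches:

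| K (assumed) | Tests, either approach | Chance of at least one false positive |
|---|---|---|
| 5 | 10 | 40% |
| 10 | 20 | 64% |
| 20 | 40 | 87% |
| 40 | 80 | 98% |

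Only interactions or further candidate factors would add tests, and the text mentions neither.

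**2. How confounding could look, by hand.** Assumed: diagnosis has no effect; higher-than-expected use in 50% of severe and 25% of non-severe participants (odds 1 v 1/3, a threefold ratio); 60% of CP and 30% of ABI are severe.

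- CP: 0.6 × 0.50 + 0.4 × 0.25 = 0.40
- ABI: 0.3 × 0.50 + 0.7 × 0.25 = 0.325
- Crude odds ratio: (0.40/0.60) / (0.325/0.675) = 1.38, where the severity-specific value is 1.0

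Precision with 50 CP and 30 ABI: expected counts are 20 and 30 in CP, 9.75 and 20.25 in ABI. The standard error of the log odds ratio is √(1/20 + 1/30 + 1/9.75 + 1/20.25) = 0.49, so the 95% interval around 1.38 is about 0.54 to 3.6. The bias, ln 1.38 = 0.33, is about two-thirds of one standard error.

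**3. Simulation with the planned group sizes.** Inputs: 30 ABI and 50 CP (article), taking the analysis to be among LIFEspan participants. Assumed: a three-level use outcome that depends on binary severity only, with no diagnosis effect. Severity raises the log-odds of higher v expected use by 1.0 or 1.6 and lowers the log-odds of lower v expected use by half that amount. The diagnosis test was run unadjusted and stratified by severity, with generalised Mantel-Haenszel standing in for polytomous regression (4000 runs per setting, two-sided 0.05). Rejection rates for diagnosis:

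| Severe, ABI / CP (assumed) | Log-odds 1.0: unadjusted, adjusted | Log-odds 1.6: unadjusted, adjusted |
|---|---|---|
| 50% / 50% | 4.2%, 4.2% | 3.8%, 4.2% |
| 35% / 60% | 8.1%, 4.8% | 13.1%, 4.7% |
| 25% / 65% | 12.1%, 5.0% | 26.4%, 5.3% |
| 20% / 80% | 22.8%, 5.0% | 55.2%, 4.4% |

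Inflation appears only when severity is unbalanced, and grows with the imbalance and the severity effect. Stratifying by severity removes it.

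**The case against.** The stated reason governs two clauses, and one of them is right: an analysis with many comparisons should be called exploratory. The article does not say outright that univariate models cut the number of tests. It does not say which larger models it was avoiding either; the charts also record cognition, communication, ambulation and living arrangements, and models with interactions or selection among many factors would add comparisons. This stands, and it limits the first part of the point to the two factors actually named.

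The term *univariate* could mean one outcome per model, in which case both factors may enter together and the confounding concern falls away. This also stands: the concern is conditional on the more usual one-predictor reading. Neither reading reduces the tests for the two factors.

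The aim is association, and a crude association is a legitimate descriptive answer to whether one diagnosis group receives more than LIFEspan foresees. Hence the univariate results should stay. They fall short only when read as showing which of the two factors matters.

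Eighty participants spread over several outcome categories could justify small models. That is a fair practical reason, though not the one given, and it limits how far adjustment can go.

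A reader might infer that the plan relies on exact p-values to control multiplicity. The text does not support this: exact values only replace threshold reporting. A reader might also take the service-use comparison to be the health care utilization analysis. That is a separate Poisson model, already adjusted for disability and severity.

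**Conclusion.** The point holds in a limited form. For degree of disability and diagnosis, the univariate restriction leaves the number of tests at 2K, as a joint main-effects model would; what properly handles multiplicity here is the exploratory label. On the one-predictor reading, a severity difference between ABI and CP could pass for a diagnosis association, or the reverse.

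It is tempting to conclude that the analysis is confounded by a known amount. The article does not support that, because it gives no severity split by diagnosis and no effect sizes. The crude odds ratio of 1.38 and the 8% to 55% rejection rates rest wholly on assumed values, and with balanced severity the problem is absent. Primary and secondary outcome analyses are untouched. Severity is minor; this is a cheap improvement to an exploratory analysis.

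**What to change.** Keep the univariate results and the exploratory label. State that univariate means one predictor per model, if that is intended. For each service variable where cell counts allow, add a polytomous model with diagnosis and degree of disability entered together, merging sparse categories if needed, and report adjusted beside unadjusted odds ratios with confidence intervals. Define a degree-of-disability grading that is comparable across ABI and CP; the only scale the article names as an example is a gross-motor one. Reword the rationale so that the multiplicity caveat rests on the exploratory label and not on the univariate restriction.

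The cost is modest, since diagnosis and severity are already to be abstracted from charts, but it is not nil. Each added severity level uses one parameter per non-reference outcome category, intervals will widen, and with 30 ABI and 50 CP participants some models may not be estimable. Where that happens, report the unadjusted result and say that diagnosis and severity could not be separated.

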#### Qualitative analyses

Transcribed data will be inputted into NVivo® software to support the qualitative data analysis. General guiding questions and a semi-structured design will support the emergence of categories and codes *a posteriori*. The analyses will begin by each investigator independently reading each transcript several times. Through inductive analysis and an iterative process of organizing the data, patterns and themes will be identified. Through group discussion and consensus, codes will be clustered by topic and connections identified between common themes to form super-ordinate themes. The transcripts will be subsequently re-examined and coded according to the thematic branches identified during these preliminary stages. Using a constant comparative approach with continual adjustment throughout the process, codes will be examined, compared, and merged, relabeled or split as necessary. Codes resulting from this open coding process will be reviewed with reference to structure and relations between them. Finally, an advanced level of coding will be conducted which aims to reorganize the data segments and assign those with similar meanings to a new category. Code-recode and peer examination will help establish the trustworthiness of theme identification and coding.

### Compensation

All participants will receive a monetary gift-card as a thank you for their enrolment and completion of baseline data measures, followed by additional gift-cards upon completion of each additional data collection period. This is an expectation of the research ethics committee, and recognizes the value of participants’ time. Participants who complete measures on-site will also be reimbursed for their traveling expenses and provided with a light meal, if desired. Similarly, mail costs will be absorbed to support this data collection strategy.

### Dissemination

The results of the study will be disseminated in academic publications and journal special issues, reports to youth and their families, and websites maintained by various disability and transition groups, as well as knowledge translation activities involving the LIFEspan team members. The LETS study project team included several knowledge users as investigators, whose interdisciplinary perspectives contributed to the design of the study from the outset and will serve to facilitate knowledge translation as the project rolls out and findings become available.

## Discussion

The LETS study will be unique in conducting a prospective examination of a recently funded coordinated long-term approach to care. Demonstration of outcomes experienced by LIFEspan clients will quantify the value of a coordinated transfer approach and provide data for future studies examining the long-term implications of such a model on continuity of care, quality of life, inclusion, and participation. In a recent paper, McDonagh and Kelly
[19] attributed the current state of transition research in part to methodological challenges. Through a chronic illness lens, they identified key issues that have hindered development of a strong evidence base for the field of transition in solid organ transplantation, including a lack of consensus on basic terminology and adolescent age criteria, a lack of suitable measurement tools, the presence of heterogeneous financial and socio-cultural demographics, and in particular, the absence of guiding theoretical research frameworks to address “the complex multidimensional, multidisciplinary, and multiagency nature” (p. 690) of transition
[19]. McDonagh and Kelly’s careful consideration of such challenges is validating for transition researchers attempting to make headway. Based on our experiences as a multidisciplinary team of pediatric and adult rehabilitation clinicians and researchers, we argue that these issues are not unique to transplantation but are common to the field of health care transition for youth with complex chronic conditions and disabilities broadly
[27,28,59]. The current paper describes similar methodological challenges. We continue this discussion by providing concrete examples of such issues and the strategies used to address them as they were encountered in designing an active longitudinal study.

Despite these challenges, the LETS study has a number of methodological strengths. Unlike previous retrospective cross-sectional studies reported in the chronic condition and disability literature to-date
[9,29-32,34,35], this prospective longitudinal study will examine the preparation for transition as well as their outcomes within one year post-transition. The outcome component of this study will determine whether LIFEspan establishes continuity of care within the first year post-transition, which is an important first step in maintaining long-term health. This window of time is previously unaccounted, as Young et al.’s study
[14] examined a longer time frame (5 – 15 years) and did not provide information on the transition itself or its immediate consequences. Second, while there are no available measures of transition readiness, we will use a combination of measures that assess skills central to successful transition and thus reflect the multidimensional approach to transition, as recommended
[19]. A wide range of measures with good psychometric properties and appropriate for individuals with disabilities will be implemented to assess outcomes such as quality of life, health, well-being, and emergency health care utilization. In addition, the qualitative component of the study will enrich this quantitative data and provide in-depth subjective perceptions of youth and their parents regarding their experiences of transition process, health care services, continuity of care, preparation interventions, etc. Finally, a comprehensive audit of implementation of LIFEspan (the process evaluation component) will allow for a detailed description of the intervention received by the participants. Previous evaluations described in the literature have not provided such detailed documentation of interventions.

Additionally, CP, ABI, and SB populations represent some of the most complex individuals who need support in transition and comprehensive, lifelong health and social services. Therefore, there is ample reason to believe that the findings from this study will generalize to a wide range of pediatric patients transitioning to adult systems. However, in general, heterogeneity is a huge issue in transition studies, due to the tremendous diversity across impairment groupings arising from variations in cognitive maturation, psychosocial development, skeletal and musculature growth, motor function and other co-morbidities
[59]. Such variations manifest themselves in very different clinical presentations with implications for self-management, multi-disciplinary treatment needs, and multi-agency service utilization
[59]. Conversely, exploring service needs and effective models of care within a single population is also extremely challenging given the vast number of potentially confounding factors associated with the potential spectrum of severity. While narrow inclusion criteria can be used to generate homogeneous samples and optimize data collection strategies, such efforts can diminish the representativeness of the sample by excluding participants who are more severely disabled, have worse health status, are least likely to achieve adequate societal participation, and who are, potentially, the most vulnerable with respect to lacking access to services that would respond to their complex needs. Thus, despite the demand for high level evidence, identification of an ethically sound and practical control group remains challenging within disability research and the field of transition
[58]. In the current study, the issue of potential differences among population groups will be addressed by using multiple baselines (i.e., participants serving as their own controls) and including a retrospective control group from the same populations as those of the intervention group. Through its inclusive design, this study will offer a unique insight in the experiences of non-verbal participants via proxy reporting and inclusion of augmentative and alternative communication users, whose transition experiences to-date have not been incorporated in formal evaluations
[60]. Studies supporting large samples and varied data collection techniques are still required as they will be critical to allow for natural variations in health and disability as well as socio-economic, geographical and cultural demographics among the youth.

Several limitations of this study should also be recognized. First, drop-out is always a significant risk in longitudinal designs. However, subject attrition for primary measures of continuity of care is expected to be minimal as permission for data release was sought at the outset of the study, and administrative database interrogation does not require continued participant contact. Unless a participant withdraws from the study, the primary outcome will be available on all participants, irrespective of loss to follow-up. In addition, key demographic data were also obtained at the time of consent; this information will allow for a detailed comparison of participants who completed the study with those that did not. However, subject attrition will still be concerning for secondary measures. Second, since this project is a longitudinal prospective cohort study of the LIFEspan model, the representativeness of the sample is also a potential risk. At present, the LIFEspan model is only available for clients of one pediatric centre. The centre is recognized as Canada’s largest rehabilitation centre and is located in a large multi-cultural urban area of Ontario. As such, LIFEspan does set the stage for an ideal model for which to strive in service delivery, where, for example, LIFEspan clients benefit from a publicly funded health care system and transportation services to and from the centre. However, generalizability of the LETS study is thereby somewhat limited, as these services and such multicultural populations might not be found in other jurisdictions. Third, the inclusion of three different disability groups also does raise the possibility of differences arising as a function of disability-related influences and not the intervention. While the standardized measures in this study have been selected based on their appropriateness for completion by people with disabilities, it is well recognized that individuals with physical and developmental disabilities may not follow the same developmental trajectory as their age-matched peers and as such, normative milestones may not be valid
[61].

While there is a wealth of evidence articulating challenges to implementing effective models of care, empirical evidence addressing processes and outcomes of transition remains limited. The importance of continuing research on adolescent health care transitions is indisputable for both practice and policy development, since due to a multitude of factors related to systemic deficiencies and inadequate preparation of clients for transition to adulthood, adolescents with childhood-onset disability are at an increased risk of health problems, secondary disabilities, and failure to achieve optimal adult societal roles and community participation. Generally, the population of young adults with disabilities and complex chronic conditions and their families will benefit greatly from stronger partnerships between the pediatric and adult sector, consistent financing, and dedicated human resources
[3]. However, there is a lack of written institutional guidance or policy regarding transition to influence such decisions, as existing research has not yet translated into policy
[5,62]. Thus, systematic evaluations are essential to determine the success of transition programs and address this gap. The LETS study is unique in design, aims to address gaps in the literature, and will provide evidence to support the expansion of the LIFEspan model and its adaptability to other organizations, within different clinical settings, and for clients with other childhood disabilities. The current paper serves as an important step in the dissemination of the results by outlining the project background, explaining its key concepts, and providing a detailed description of methods adopted prior to the results of the analyses.

